## Abstract

**Background:**

Caesarean scar pregnancy (CSP) is a type of ectopic pregnancy where the fertilised egg is implanted in the muscle or fibrous tissue of the scar after a previous caesarean section. Management options for women who opted for termination of CSP include sharp curettage, dilation and evacuation (D&E), excision of trophoblastic tissues, local or systemic administration of methotrexate, bilateral hypogastric artery ligation, and selective uterine artery embolisation with curettage and/or methotrexate administration. Recently hysteroscopic resection has also been proposed as an alternative option.

**Objective:**

To compare the surgical outcome of hysteroscopic resection with dilation and evacuation (D&E) for the treatment of caesarean scar pregnancy (CSP).

**Methods:**

Parallel-group, non-blinded, randomised clinical trial conducted at a single centre in Italy. Eligible women are those with singleton gestations at less than 9 weeks of gestation, and with thickness of myometrial layer ≥1 mm at the level of the ectopic. Inclusion criteria are women with CSP with positive embryonic/fetal heart activity who opted for termination of pregnancy. Patients will be randomised 1:1 to receive either hysteroscopic resection (i.e. intervention group) or D&E (i.e. control group). In both groups, 50 mg/m2 (based on DuBois formula for body surface area) of methotrexate (MTX) will be injected intramuscularly at the time of randomisation (day 1) and another dose at day 3. A third dose of MTX is planned in case of persistence of fetal heart activity on day 5. Participants will receive either D&E or hysteroscopic resection from 3 to 7 days after the last dose of MTX. A sample size of 54 women is planned.

**Main Outcome Measures:**

The primary outcome is the success rate of the treatment protocol, defined as no requirement for further treatment until complete resolution of the CSP as demonstrated by negative beta hCG levels and absence of residual gestational material on ultrasound examination..

**Study hypothesis:**

Hysteroscopic surgery is superior to D&E for the treatment of CSP.

**What is new?:**

The results of the trial will provide information on the best treatment for CSP.

## Introduction

Caesarean scar pregnancy (CSP) is a type of ectopic pregnancy where the fertilised egg is implanted in the muscle or fibrous tissue of the scar after a previous caesarean section (Timor-Tritsch et al., 2019). There are two types of CSP; CSP with growth towards the cervicoisthmic space or uterine cavity (type I, endogenic type) and those with deep invasion of scar defect and growth towards the bladder and abdominal cavity (type II, exogenic type) (Gonzalez et al., 2017).

Expectant management is acceptable in CSP with no fetal cardiac activity (Jayaram et al., 2018), while CSP with positive embryonic/fetal heart activity managed expectantly is associated with a high burden of maternal morbidity including severe haemorrhage, early uterine rupture, hysterectomy and severe placenta accreta, raising the question whether termination of pregnancy should be the treatment of choice for these women (Cali et al., 2018). Several approaches have been studied for the management of CSP in women who opted for termination of pregnancy, including sharp curettage, dilation and evacuation (D&E), excision of trophoblastic tissues, local or systemic administration of methotrexate, bilateral hypogastric artery ligation, and selective uterine artery embolisation with curettage and/ or methotrexate administration (Karahasanoglu et al., 2018). Recently, operative hysteroscopy with resection, has been proposed as a safe and effective alternative for the treatment of CSP (Qian et al., 2015; Fylstra, 2014). Operative hysteroscopy has many advantages compared to the traditional blind approach and has continued to grow for management of different conditions, including retained products of conception (Alonso Pacheco et al., 2019), or incomplete abortion (Golan et al., 1992).

## Objective

The aim of this trial is to compare the success rate of hysteroscopic resection with D&E for the treatment of CSP.

## Methods

### Study design and participants

This is a single-centre parallel group randomised controlled trial (RCT) of women with CSP who opt to have termination of pregnancy using either hysteroscopic resection or D&E at the University of Naples Federico II (Naples, Italy).

The trial was approved by the local ethics committee. All participants in the trial provided written informed consent.

Eligible women are those who opt to have termination of pregnancy with singleton gestations of less than 9 weeks gestation with positive embryonic/ fetal heart activity and with ≥1 mm myometrial thickness overlying the pregnancy . Both type I and type II CSP are included. Exclusion criteria are multiple gestations, heterotopic pregnancy, diagnosis of cervical pregnancy, failing intrauterine pregnancy or any other anomalous implantation site, negative fetal heart activity at the time of randomisation and myometrial thickness of <1 mm.

### Randomisation and masking

Eligible participants will be randomised 1:1 to receive either hysteroscopic resection (i.e. intervention group) or ultrasound-guided D&E (i.e. control group). Randomisation will be via a web- based system that is prepared by an independent statistician. The recruiters and the trial coordinator do not have access to the randomisation sequence. The trial is open label but the data analysts will be blinded to allocated treatment group.

### Interventions

50 mg/m2 (based on DuBois formula for body surface area) of methotrexate (MTX) (Du Bois and Du Bois, 1989; Kutuk et al., 2014) will be injected intramuscularly to all participants in both groups at the time of randomisation (day 1) and another dose on day 3. A third dose of MTX is planned in case of persistence of positive fetal heart activity on day 5.

Women in the control group will receive D&E from 1 to 5 days after the last dose of MTX. D&E is performed under ultrasound guidance under spinal anaesthesia. A speculum is placed in the vagina to see the cervix and a tenaculum is placed to steady the cervix. The cervix is dilated using Hegar dilators. After sufficient dilation, sharp curettage with or without suction evacuation with Karman cannula, is performed (Stubblefield 1986).

Women in the intervention group will receive hysteroscopic resection from 1 to 5 days after the last dose of MTX. Hysteroscopic resection will be performed under spinal anaesthesia (Giampaolino et al. 2018), using 15 Fr bipolar miniresectoscope. All included women are admitted for inpatient management.

### Diagnosis of caesarean scar pregnancy

Diagnosis of CSP is made by transvaginal ultrasound using the following criteria as described by Timor-Tritsch et al. (2012); visualisation of an empty uterine cavity and empty endocervical canal; detection of the placenta and/or gestational sac embedded in the hysterotomy scar; triangular gestational sac that fills the niche of the scar; a thin myometrial layer (1-3 mm) between the gestational sac and the bladder; a closed and empty cervical canal; presence of embryonic/fetal pole; presence of a prominent and at times rich vascular pattern at or in the area of the caesarean scar in the presence of a positive pregnancy test.

### Outcomes

The primary outcome is the success rate of the treatment protocol, defined as no requirement for further treatment until complete resolution of the CSP as demonstrated by negative beta hCG levels and absence of residual gestational material on ultrasound examination. Treatment failure is defined as the need for further treatment before complete resolution of the CSP. Secondary outcomes are use of additional procedures, intra- and postoperative complications, blood transfusions, admission to intensive care unit (ICU), maternal death and length of stay (LOS) in the hospital.

### Sample size calculation

The sample size calculation was based on detecting an effect that produces an increase in the primary outcome from a baseline successful rate of 65% (women undergoing D&E) (Kanat-Pektas et al., 2016) to a success rate of 95% (women undergoing hysteroscopy surgery) (Ash et al., 2007; Deans and Abbott, 2010; Birch Petersen et al., 2016). Given an alfa of 0.05 and 80% power, a sample size of 54 women is planned (27 for each intervention group).

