### Statistical analysis

Univariate comparisons of dichotomous data will be performed with the use of the chi-square test with continuity correction. Comparisons between groups will be performed with the use of the T-test to test group means by assuming equal within- group variances.

The primary analysis will be an intention to treat comparison of the treatment assigned at randomization. The effect of hysteroscopic resection on the cumulative incidence of each outcome will be quantified as the relative risk (RR) and its 95% confidence interval (CI). A 2-sided P value less than .05 was considered significant.

Statistical analysis was performed using Statistical Package for Social Sciences (SPSS) v. 19.0 (IBM Inc).

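### With the continuity-corrected chi-square test that the protocol names, 27 women per arm give about 71.5% power, not the stated 80%

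*Protocol article*

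**What the plan says.** All references are to the protocol article.

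- **Sample size calculation.** The assumed rates run from a "baseline successful rate of 65% (women undergoing D&E" "to a success rate of 95% (women undergoing hysteroscopy surgery". The target follows: "Given an alfa of 0.05 and 80% power, a sample size of 54 women is planned (27 for each intervention group". No formula or test is named.
- **Outcomes.** "The primary outcome is the success rate of the treatment protocol", so each woman is either a success or a failure.
- **Statistical analysis.** "Univariate comparisons of dichotomous data will be performed with the use of the chi-square test with continuity correction". The significance rule is "A 2-sided P value less than .05 was considered significant". No other test is named for binary outcomes; the effect measure is a relative risk with a 95% confidence interval.
- **Randomisation and masking.** "Eligible participants will be randomised 1:1", so the arms are of equal size.

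**The concern.** A power figure belongs to a particular test. The 80% is stated in one section and the test in another, and in samples this small a continuity correction costs a good deal of power. If 27 per arm came from a calculation without the correction, the trial as it will be analysed is weaker than stated.

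This could decide the result. Take 26 of 27 successes on hysteroscopy and 20 of 27 on D&E, a difference of 22 percentage points. There are 46 successes and 8 failures in all, and the cross-product difference is 26×7 − 20×1 = 162.

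- Without correction: 54 × 162² / (27 × 27 × 46 × 8) = 5.28, above the critical value of 3.84.
- With correction: 54 × (162 − 27)² / (27 × 27 × 46 × 8) = 3.67, below it.

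The discussion section calls the condition rare and the trial the first randomised comparison of these two procedures after methotrexate. A false negative may not soon be put right by another trial.

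**Working it through.** **Inputs.** Success rates 0.65 and 0.95, alpha 0.05, power 0.80 and 27 per arm (Sample size calculation); two-sided testing and the continuity-corrected chi-square (Statistical analysis); 1:1 allocation (Randomisation and masking). Difference d = 0.30 and mean rate 0.80.

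**1. Reproducing the plan's figure.** Pooled-variance formula without correction:

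n = [1.96 × √(2 × 0.8 × 0.2) + 0.8416 × √(0.65 × 0.35 + 0.95 × 0.05)]² / 0.30² = (1.1087 + 0.4413)² / 0.09 = 26.70, rounded up to 27.

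This matches the protocol exactly. Other variants do not:

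| Formula | n per arm |
|---|---|
| Two-sided, with continuity correction | 34 |
| One-sided, uncorrected | 21 |
| One-sided, corrected | 28 |
| Two-sided, unpooled variance | 24 |
| Two-sided, arcsine | 24 |

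**2. Formula for the test the plan names.**

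n = (26.70 / 4) × [1 + √(1 + 4 / (26.70 × 0.30))]² = 33.03, rounded up to 34.

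**3. Approximate power at 27 per arm.** The null standard error is √(0.32/27) = 0.1089, and 1.96 times that is 0.2134. The standard error under the alternative is √(0.275/27) = 0.1009.

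- Uncorrected: (0.30 − 0.2134) / 0.1009 = 0.858, power 80.5%.
- Corrected (subtract 1/27 = 0.0370): (0.30 − 0.0370 − 0.2134) / 0.1009 = 0.491, power 68.8%.

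**4. Exact power at 27 per arm.** Power is the sum of Binomial(27, 0.95) × Binomial(27, 0.65) over the 28 × 28 tables that each test rejects. Type I error is the maximum over a common success rate.

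| Test at two-sided 0.05 | Exact power | Maximum type I error |
|---|---|---|
| Continuity-corrected chi-square (the plan) | 71.5% | 0.026 (0.019 at a common rate of 80%) |
| Fisher's exact | 71.5% | – |
| Boschloo's unconditional exact | 81.5% | 0.045 |
| N−1 chi-square | 84.2% | 0.054 |
| Uncorrected Pearson chi-square | 85.9% | 0.057 |

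**5. Exact power of the corrected test by n per arm.** 25: 65.6%; 27: 71.5%; 30: 78.8%; 31: 80.7%; 34: 85.8%. The first size to reach 80% is 31 per arm, 62 in total. The formula's 34 is therefore conservative; on the exact scale the shortfall is 4 women per arm.

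**The case against.** The strongest points on the other side are these.

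- **The cause is inferred.** The sample-size section names no formula. This is right, and the exact match at 27 is only strong evidence. But the 71.5% does not depend on it: it follows from the stated n, rates, alpha and test.
- **The test sentence is generic.** The paragraph on the primary analysis speaks of an intention-to-treat comparison and a relative risk with its interval. If success were judged by whether a log-scale Wald interval for the relative risk of success excludes 1, exact power would be 81.9% with maximum size 0.045. That interval method is an assumption, and with the relative risk taken on failure the power falls to about 49%. The corrected chi-square is still the only named test that yields the P value for this outcome.
- **The error is conservative.** It neither inflates type I error nor biases the estimate, and modest changes in the planning rates matter more: the corrected test has 54.8% power at 70% versus 95%, and 47.3% at 65% versus 90%. That is fair as perspective, but it does not make the stated 80% correct at the stated rates.
- **Some protection is bought.** The Pearson and N−1 tests do exceed 5% slightly. This stands against those two, but not against Boschloo's test, which stays below 5% and still exceeds 80% power.
- **Timing is uncertain.** The article mixes future and past tense, so it does not show whether outcomes had been seen. This limits which fix is open, as set out below.

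**Conclusion.** The concern holds. At the protocol's own rates, alpha and sample size, its named test has 71.5% exact power (68.8% by the normal approximation), which is 8.5 to 11 points below the stated 80%. The chance of missing the assumed 30-point benefit is 28.5% instead of 20%, a relative increase of 28.5 / 20 − 1 = 43%.

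The result assumes that the corrected chi-square decides the primary outcome and that all 54 women have an outcome. The documents give no attrition rate; if, as an illustration, 25 per arm were evaluable, power would be 65.6%. Because the stated power for the primary outcome is wrong as written, and a change of test after the results are known would be post hoc, it should be corrected before the analysis.

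**What to change.** **If outcomes have not been analysed:** keep 54 women, name Boschloo's unconditional exact test at two-sided 0.05 for the primary outcome, and state its exact power of 81.5% (maximum type I error 0.045) in the sample-size section. This takes one sentence in each of the two sections and no extra patients. The test needs R or Python in place of the SPSS 19 named in the protocol.

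**If the corrected test is kept, or outcomes have already been seen:** leave the test as it is and restate the power as about 71%. This costs one sentence. Holding 80% with the corrected test would instead take 31 per arm by exact calculation (62 in total, 8 more women), or 34 per arm by the formula (68 in total, 14 more).

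Fisher's exact test is no remedy, since its power is the same 71.5%. The N−1 chi-square is available in SPSS (for a 2×2 table it is the linear-by-linear association statistic), but its maximum type I error is 0.054 at 27 per arm and 0.065 at 25 per arm, so it is a second choice.

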### Statistical analysis

Univariate comparisons of dichotomous data will be performed with the use of the chi-square test with continuity correction. Comparisons between groups will be performed with the use of the T-test to test group means by assuming equal within- group variances.

The primary analysis will be an intention to treat comparison of the treatment assigned at randomization. The effect of hysteroscopic resection on the cumulative incidence of each outcome will be quantified as the relative risk (RR) and its 95% confidence interval (CI). A 2-sided P value less than .05 was considered significant.

Statistical analysis was performed using Statistical Package for Social Sciences (SPSS) v. 19.0 (IBM Inc).

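### The primary comparison is fixed as a univariate, continuity-corrected chi-square although both scar-pregnancy types are enrolled; an uncorrected test stratified by type would be more powerful and more robust with the same 54 women

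*Protocol article*

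**What the plan says.** The Introduction separates endogenic CSP, growing towards the cavity, from "those with deep invasion of scar defect and growth towards the bladder and abdominal cavity (type II, exogenic type"). Under Study design and participants, "Both type I and type II CSP are included".

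Under Statistical analysis, "Univariate comparisons of dichotomous data will be performed" with a continuity-corrected chi-square. The primary analysis is by intention to treat, the effect measure is a relative risk with 95% CI, and "A 2-sided P value less than .05 was considered significant". No adjustment for CSP type is mentioned. Randomisation and masking describes 1:1 web-based allocation and names no stratification factor, but does not rule one out.

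The sample size assumes "a baseline successful rate of 65% (women undergoing D&E") rising "to a success rate of 95% (women undergoing hysteroscopy surgery"). "Given an alfa of 0.05 and 80% power", "a sample size of 54 women is planned (27 for each intervention group").

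**The concern.** Both procedures are carried out through the cervix, and success requires both that no gestational tissue remains on ultrasound and that no further treatment is needed. Tissue growing away from the cavity is plausibly harder to clear by that route. Diagnosis is by transvaginal ultrasound, so type can reasonably be recorded before randomisation. The stated comparison does not use it.

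Two things are at stake in a trial of 54 women with a rare condition. First, the arms may by chance differ noticeably in their share of type II. Readers would then dispute the result, and an adjustment chosen after seeing the data would carry little weight. Second, the stated test spends only about half of the allowed type I error, so power is lost for no benefit.

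**Working it through.** **Inputs from the article.** Success 65% and 95%; two-sided alpha 0.05; power 80%; 27 per arm; chi-square with continuity correction.

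**Assumptions (the article gives no figures).** Type II share 20% to 50%. Gap in success between types in the D&E arm 0 to 37.5 points, with a hysteroscopy gap one fifth as large. Average success is held at 65% and 95%.

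**Step 1: reproduce the planned size.** Pooled formula without correction, mean rate 0.80:

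n = [1.960 × √(2 × 0.80 × 0.20) + 0.842 × √(0.65 × 0.35 + 0.95 × 0.05)]² / 0.30² = 26.7, so 27 per arm and 54 in total. This matches. The same formula with continuity correction gives 34 per arm (68). The size was therefore set without the correction that the analysis applies.

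**Step 2: the stated test.** With a, b successes and failures in one arm, c, d in the other, S and F total successes and failures, and N = 54:

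- corrected: 54 × (|ad − bc| − 27)² / (27 × 27 × S × F)
- N-1: 53 × (ad − bc)² / (27 × 27 × S × F)

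Illustration: 25/27 against 19/27 gives ad − bc = 25 × 8 − 2 × 19 = 162, S = 44, F = 10. Corrected: 54 × 135² / 320,760 = 3.07. N-1: 53 × 162² / 320,760 = 4.34. The critical value is 3.84, so only the N-1 test rejects.

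Summing binomial probabilities over all tables:

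| Test | Power, 65% vs 95% | Type I error, both arms 65% |
|---|---|---|
| Corrected chi-square (stated) | 71.5% | 0.026 |
| N-1 chi-square | 84.2% | 0.050 |

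Dropping the correction gains 84.2 − 71.5 = 12.7 points.

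**Step 3: stratify by type.** The Cochran-Mantel-Haenszel statistic without correction is (ΣOₖ − ΣEₖ)² / ΣVₖ over the two types. Oₖ is the number of successes in one arm, Eₖ = m₁ₖSₖ/Tₖ and Vₖ = m₁ₖm₂ₖSₖFₖ / [Tₖ²(Tₖ − 1)], with m₁ₖ, m₂ₖ the arm sizes, Sₖ, Fₖ the successes and failures, and Tₖ the total in type k. Simulation, 400,000 trials per row, 40% type II:

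| D&E gap by type | Stated test | N-1 | CMH, uncorrected | CMH minus N-1 |
|---|---|---|---|---|
| 0 | 71.5% | 84.2% | 83.6% | −0.7 |
| 10 | 71.5% | 84.1% | 83.7% | −0.5 |
| 20 | 71.7% | 84.2% | 84.3% | +0.1 |
| 30 | 71.6% | 84.1% | 85.3% | +1.1 |
| 37.5 | 71.4% | 84.1% | 86.3% | +2.2 |

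Differences are taken before rounding. Over 20% to 50% type II, CMH power runs from about 83% to 87%, and repeat runs put the last column between about −0.8 and +2.5. With 65% success in both arms, CMH type I error is 0.048 to 0.050; the stated test stays at about 0.026.

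**Step 4: chance imbalance.** With each woman's type drawn at random and no stratified allocation, the arms differ in type II share by 20 points or more in 6.0%, 10.1%, 12.6% and 13.4% of trials at 20%, 30%, 40% and 50% type II. If the total number of type II women is held fixed, the range is 4% to 17%.

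Under the 37.5-point D&E gap (7.5 points for hysteroscopy), a 20-point imbalance split evenly moves the risk difference by 0.10 × 37.5 + 0.10 × 7.5 = 4.5 points, or 15% of the planned 30. It reaches 0.20 × 37.5 = 7.5 points only if the whole imbalance falls in the D&E arm.

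**The case against.** The strongest reply is that nothing here is invalid. Under randomisation the unadjusted intention-to-treat comparison is sound, and chance imbalance is already allowed for in its p-value and CI. In null simulations its type I error stays near 0.026 even with a 37.5-point type gap. This stands, so the point cannot be put as a bias.

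Three further parts of the reply also stand.

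- A reader might infer that type is a strong prognostic factor. The article describes the types only anatomically, and the 37.5-point gap is an assumption at the high end.
- A reader might credit stratification with the whole rise in power. Nearly all of it comes from dropping the correction. With the correction kept in both tests at 40% type II, stratifying gives 70.5% against 71.5% with no gap, and 74.4% against 71.4% at 37.5 points.
- A reader might infer that allocation ignores type, or that no adjusted analysis exists. The article is silent on both, and such details may sit in the full protocol or analysis plan.

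The reply does not remove the point, because the article is not silent on the test: it names a univariate, continuity-corrected chi-square.

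**Conclusion.** The point holds as an improvement in efficiency and robustness. At the planned rates and 27 per arm, the stated test has about 71.5% power at a type I error of about 0.026. The uncorrected test stratified by type has about 83% to 87% at about 0.05. It beats the stated test whether or not type matters, because about 12.7 points of the gain do not depend on type.

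The contribution of type itself is small and uncertain: about −0.8 to +2.5 points of power against an unadjusted N-1 test, breaking even near a 20-point D&E gap, plus protection against an imbalance that would occur in roughly 6% to 13% of trials. These ranges rest on the assumed type II share and type effect, since the article supplies neither. The 71.5% and 0.026 rest only on the article's own figures, the latter at 65% success in both arms.

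**What to change.** In Statistical analysis, make the primary test a Cochran-Mantel-Haenszel test stratified by CSP type (I or II), without continuity correction. Report the Mantel-Haenszel relative risk and risk difference with 95% CIs, and keep the unadjusted N-1 chi-square as supportive. Record type from the diagnostic ultrasound before allocation, and date the change before anyone sees outcomes by arm.

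As a suggestion only: if allocation is not already stratified by type, add type as a stratum for women not yet randomised.

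The cost is a few sentences of analysis wording and one data field, with no extra women. The downsides are a loss of under 1 point of power against the N-1 test if type is not prognostic, and possibly one small stratum, which the Mantel-Haenszel method tolerates.

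### The t-test fixed for comparing means assumes equal variances, which the trial's own planning rates make doubtful for length of stay. Welch's test removes the assumption at no cost (minor).

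*Protocol article*

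**What the plan says.** The Statistical analysis section assigns dichotomous data to a chi-square test with continuity correction and then says: "Comparisons between groups will be performed with the use of the T-test to test group means by assuming equal within- group variances". It gives no check of that assumption and no alternative. The significance rule is "A 2-sided P value less than .05 was considered significant".

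The sentence names no outcome. The Outcomes section lists the primary outcome (treatment success, yes or no) and secondary outcomes that read as events, ending with "maternal death and length of stay (LOS) in the hospital". Length of stay is the only one that is naturally a continuous quantity, so the t-test sentence applies to it in practice.

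The Sample size calculation section plans for a change from a "baseline successful rate of 65% (women undergoing D&E") "to a success rate of 95% (women undergoing hysteroscopy surgery"), with 27 women per group. The document gives no mean, SD or distribution for length of stay.

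**The concern.** The pooled t-test uses one common variance for both arms. The planning rates imply that about a third of D&E women and one in twenty hysteroscopy women need further treatment. If that treatment adds hospital days, the D&E arm mixes short and long stays while the hysteroscopy arm is nearly homogeneous. Equal spread is then hard to reconcile with the effect that the trial is designed to find.

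What is at stake is the calibration of one secondary comparison: its p-value and any confidence interval for the difference in mean stay. The pooled standard error is robust to unequal spread when the arms are equal in size. It is too small when the more variable arm is the smaller one, and too large when it is the larger one.

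**Working it through.** **1. The plan's own figure.** The only figure to reproduce is the sample size. With p1 = 0.65, p2 = 0.95, mean 0.80, two-sided alpha 0.05 and 80% power:

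n = [1.960 × √(2 × 0.80 × 0.20) + 0.842 × √(0.65 × 0.35 + 0.95 × 0.05)]² / 0.30² = [1.109 + 0.441]² / 0.09 ≈ 26.7, so 27 per arm and 54 in total.

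The stated 54 reproduces. It does not involve length of stay.

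**2. Spread implied by the planning rates.** Further treatment is needed by 1 − 0.65 = 35% and 1 − 0.95 = 5%. If each failure adds a fixed number of days D, that component has variance D² × p(1 − p):

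- D&E: 0.35 × 0.65 = 0.2275 (times D²)
- hysteroscopy: 0.05 × 0.95 = 0.0475 (times D²)
- SD ratio: √(0.2275 / 0.0475) = √4.789 = 2.19

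Other variation dilutes this ratio. In a simulation, stay after the procedure was assumed lognormal (median 2 days, log-SD 0.4), with an average of 2, 5 or 10 extra days per failure. The SD ratios were 1.4, 1.9 and 2.2. Adding an assumed common pre-procedure wait lowers them to 1.1, 1.5 and 1.9. So 2.19 is close to the upper end.

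**3. Why arm sizes decide the effect.** Set the variance to 4.789 in the more variable arm and 1 in the other, and compare the true variance of the mean difference with what the pooled formula expects.

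- 27:27. True: 4.789/27 + 1/27 = 0.214. Pooled: (4.789 + 1)/2 × 2/27 = 0.214. No bias.
- More variable arm 22, other 32. True: 4.789/22 + 1/32 = 0.249. Pooled: (21 × 4.789 + 31)/52 × (1/22 + 1/32) = 2.530 × 0.0767 = 0.194. Ratio 0.78, so the test is too liberal.
- More variable arm 32, other 22. True: 4.789/32 + 1/22 = 0.195. Pooled: (31 × 4.789 + 21)/52 × 0.0767 = 3.259 × 0.0767 = 0.250. Ratio 1.28, so the test is too conservative.

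**4. Type I error by simulation** (normal data, equal means, nominal 5%; SD ratio 2.19 in the unequal splits):

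| Arms | Pooled | Welch |
|---|---|---|
| 27:27 | 5.0–5.4% | 4.9–5.1% |
| 29:25, smaller arm more variable | about 6% (6.1–6.5% across runs) | about 5% |
| 32:22, smaller arm more variable | 8.4% | 4.9% |
| 32:22, larger arm more variable | 2.9% | about 5% |

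**5. How likely are unequal arms?** The article gives a 1:1 ratio but does not say whether randomisation is restricted. Under simple randomisation (an assumption), a split of 32:22 or worse has probability 22%, or 11% in a given direction.

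**6. Cost of Welch.** In the lognormal scenarios with 27 per arm (medians 2 and 3 days, log-SD 0.4 to 0.8), replacing pooled by Welch changed power by less than 1 percentage point.

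**The case against.** **The effect is negligible at the planned sizes.** This stands. At 27:27 the two tests are practically the same, and 32:22 is a selected case. The point is a safeguard, not a demonstrated error.

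**If the spread differs only because the treatments differ, it is equal under the null and the pooled test keeps its error rate.** This is fair for the p-value under a strict null. It does not rescue the confidence interval: with normal data, its coverage depends on the variances and arm sizes, not on the true mean difference.

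**Failures need not lengthen the index stay.** This also stands. Failure is defined by further treatment before complete resolution, and the document does not say that it occurs during the admission. The unequal spread is therefore conditional.

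**Welch does not cure skewness.** True. With equal means, strong skew and SD ratios of 2.3 to 4.3 at 27:27, pooled gives 7.1% to 10.9% and Welch 7.0% to 10.6%.

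A reader might infer more than the document supports:

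- *That length of stay is known to be skewed.* No distribution is given. Skew is plausible, not documented.
- *That the stay includes the methotrexate phase and so buries the treatment effect.* The Interventions section says "All included women are admitted for inpatient management", but gives no admission day, and the Outcomes section does not say when the stay starts. A condensed article may leave that to the full protocol. Any power loss computed from it rests on assumed stays and an assumed start. Including a common wait would also make the spreads more equal.
- *That the clock should start at surgery.* That origin lies after randomisation and is undefined for a woman who never reaches surgery, which sits badly with the intention-to-treat analysis.
- *That a Wilcoxon test is the better choice.* It does not compare means, and it loses power when a minority has long stays, the mechanism at issue here. In the scenario of step 2 with an average of 5 extra days per failure, its power was 46% against 67% for the pooled t-test.

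**Conclusion.** The point holds as a minor one. The plan fixes an assumption that it does not need and that its own 35% and 5% failure rates make doubtful for length of stay, provided further treatment prolongs the stay. The consequence depends on the final arm sizes: none of note at 27:27, about 6% at 29:25, and about 8% or 3% at 32:22, against about 5% for Welch throughout. These figures assume normal data and an SD ratio of 2.19, which is near the upper end of what the planning rates produce; smaller ratios give smaller departures. Only a secondary outcome is concerned. The documents do not support any claim about the actual shape of the stay, its starting point or its power.

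**What to change.** In the Statistical analysis section, replace the equal-variance wording with Welch's unequal-variance t-test for length of stay, and report the mean difference with its Welch 95% confidence interval. Add medians and quartiles by arm. Stay counted from the procedure may be added as a supplementary description beside total stay, but should not replace it.

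The first two changes need no new data, no extra patients and no change to the sample size; the loss of power at equal arms is under 1 percentage point in the scenarios examined. The supplementary description needs the procedure and discharge dates; the article does not say whether these are recorded.
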